#### Cost-effectiveness analysis

Finally we will analyse the cost data on the expenditure on the various intervention inputs consisting of human resources, training, community mobilization, awareness promotion materials, stationary and overheads. These costs will be compared with the outcomes (availability of key generic NCD medicines in PHC, prescription of generic medicines, regular and rational consumption of medicines among NCD patients) extrapolated at the population (NCD) level for the study arms. Incremental cost effective ratios will be estimated against the control arm.

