**Fig. 5 Fig5:**
[figure not shown]
ATM conceptual framework

Of the seven *talukas* which qualified for the intervention, we randomly chose three *talukas* using the online random number generating tool (Available at http://www.random.org/; see Additional file 2). The three *talukas* chosen were Koratagere, Sira and Turuvekere. Some characteristics of the three *talukas* are presented in Table 2. PHCs across the three *talukas* were randomly assigned to one of three arms (A, B and C) of the study intervention. In Arm A, PHCs will receive a package of interventions to optimise service delivery, while Arm B, they will receive Arm A package as well as an additional package of interventions to strengthen existing community participation platforms for organising NCD care at PHC. PHCs in Arm C will be the control. The package of activities in A, B and C are described in Table 3. A detailed description of the intervention and the underlying assumptions behind the activities proposed is provided in Additional file 3 and step-wise plan of rolling out of the intervention is presented in Fig. 6.

**Table 2 Tab2:** Characteristics of study talukas

Characteristics	Koratagere	Sira	Turuvekere
Area	652 Sq km	1552 Sq km	778 Sq km
Population	160,952	301,473	174,297
Number of private pharmacies	19	30	22
General adult literacy rate	71 %	67 %	73 %
Number of PHCs	11	17	11
Average population per PHC	14,500	18,000	16,000
Number of private hospitals/clinics	21	64	18
Number of PHCs with qualified MBBS doctors (of) total number of PHCs in *taluka* (as on March 2014)	11 of 11	15 of 17	10 of 11

(Source: Census 2011)

**Table 3 Tab3:** Description of activities planned under the study intervention arms

Intervention arm	Intervention name	Intervention input	Activities
A	Optimise service delivery	Orientation training & workshop for PHC medical officers	Training on standard treatment guidelines for NCDs, rational prescription, maintaining treatment cards for patients with NCDs and conduction of health days for NCD care.
		Training workshop for pharmacists	Training on need assessment for medicines, counselling patients on medicines and their side effects and non- drug treatment, indenting for medicines and record keeping at PHCs.

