### Survey sampling

#### Quantitative data

##### Household survey

The WHO household survey tool does not have inclusion criteria related to NCD. Sample size calculation was based on obtaining at least 30 households per PHC spread across three clusters (a, b and c with 10 households per cluster; see above). A typical PHC in Tumkur district has at least five villages in each cluster, and hence at least 1000 households in each cluster (approximately 250 households in a village). We aimed for a total of 1170 households anticipating 30 households per PHCs across the 39 PHCs.

We started the survey at the PHC where we listed all the villages under the PHC area. These villages were then divided into the three clusters based on the distance from the PHC and from each cluster, one village was randomly chosen. We randomly selected a minimum of 10 NCD households from all four directions starting from the central point of the village. After getting informed consent of the participant the survey questionnaire was administered to the NCD patient for the interview. In his/her absence, the spouse or another member of the household who was over 18 years of age, aware of the information sought in the survey and willing to provide this information was interviewed. The data collectors started the survey within each village in four different directions and ensured that all types of houses and areas within the village were included in the sampling. Wherever 10 NCD households were not obtained in one village, the data collectors repeated the process in the nearest adjoining village. Each participant was provided with an information sheet and health awareness material in local language related to NCDs (Additional file 7) as well as contact information of the research team.

We surveyed 10 households from within five kilometre radius from the PHC (cluster a), 10 from between five to 10 km radius (cluster b), and 10 from more than 10 km distance from the PHC (cluster c). All of the 39 PHCs in these three *talukas* were covered, resulting in 1069 NCD households surveyed as presented in Table 4 and Table 5. The same households shall be sampled during the endline survey planned in last quarter of 2015.

**Table 4 Tab4:** Distribution of households participating in the study by *taluka*

S No.	Taluka	Number of households interviewed
1	Turuvekere	326
2	Sira	482
3	Koratagere	261
Total		1069

**Table 5 Tab5:** Number of PHCs covered in the ATM study talukas

Taluka	Number of PHCs

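### The cost-effectiveness ratios name only the control arm as comparator, so Arm B's ratio can understate the cost of its community add-on; medicine costs are also left out for both arms

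*Protocol article*

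**What the plan says.** All references are to the Protocol article.

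- **Comparator.** The section Cost-effectiveness analysis says: "Incremental cost effective ratios will be estimated against the control arm". No ratio of Arm B to Arm A is mentioned there or elsewhere.
- **Arms.** The section on the rapid local health system assessment and choice of talukas says of the PHCs in Arm B that "they will receive Arm A package as well as an additional package of interventions to strengthen existing community participation platforms". Table 3 shows the same nesting. Patient groups and the orientation of the patient welfare committees (ARS) appear only under Arm B.
- **Costs.** The expenditure to be analysed is that on "intervention inputs consisting of human resources, training, community mobilization, awareness promotion materials, stationary and overheads". Medicines are not in the list.
- **Effects.** The same section counts availability of key generic medicines at the PHC, their prescription, and "regular and rational consumption of medicines among NCD patients".
- **Medicine supply as an activity.** Table 3 makes securing drug supply (routine supply chain, district plan or ARS funds) an Arm A activity. Under Arm B it adds orientation of ARS members on using untied funds to buy NCD medicines.
- **Status.** Table 9 lists the incremental cost-effectiveness ratio under the primary outcomes, and the last research sub-question asks for a marginal cost.

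**The concern.** With nested options, the incremental ratio of the larger package is taken against the next smaller one. A planner who already has, or could have, the Arm A package needs to know what the community package adds and at what price, and only B versus A answers that. B versus control mixes the add-on with gains that the Arm A package would have delivered anyway. The study is interested in the add-on: its first objective and second sub-question concern patient groups and community participation, which are specific to Arm B.

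The medicines point is separate and smaller. The effects count more medicine being available, prescribed and taken, while the cost list does not count that medicine, although Table 3 foresees public money buying some of it.

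At stake is a primary outcome on which planners might decide whether to pay for the community component.

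**Working it through.** **Inputs.** The documents give no unit costs, effect sizes, ratios or willingness-to-pay threshold, so there is no stated figure to reproduce. All costs and effects below are assumptions. Only the nesting of the arms, the comparator and the cost list come from the plan.

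**Algebra.** Let C_A, C_B be extra costs over control and E_A, E_B extra effects over control, with E_B > E_A > 0.

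- A vs C = C_A / E_A
- B vs C = C_B / E_B
- B vs A = (C_B − C_A) / (E_B − E_A)
- Hence B vs C = w × (A vs C) + (1 − w) × (B vs A), with w = E_A / E_B.

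B vs C therefore lies between the other two ratios. It is below B vs A exactly when the add-on is less efficient than Arm A.

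**Illustration.** Take C_A = 40,000, C_B = 90,000 and E_A = 100 extra patients on regular medication, so A vs C = 40,000/100 = 400.

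| E_B | B vs C = 90,000/E_B | B vs A = 50,000/(E_B − 100) | B vs A divided by B vs C |
|---|---|---|---|
| 95 | 947 | B dominated by A | – |
| 110 | 818 | 5,000 | 6.1 |
| 120 | 750 | 2,500 | 3.3 |
| 150 | 600 | 1,000 | 1.7 |
| 200 | 450 | 500 | 1.1 |

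Check of the identity at E_B = 120: w = 100/120 = 0.833, and 0.833 × 400 + 0.167 × 2,500 = 750.

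**Where the masking ends.** Set B vs A equal to A vs C: 50,000/(E_B − 100) = 400 gives E_B = 225, and B vs C = 90,000/225 = 400. At that effect or above, B vs C does not flatter the add-on.

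**Medicines.** If the effect is an extra patient on regular medication and each such patient uses medicine costing d to the public payer, every ratio rises by d. With E_B = 120:

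| d (assumed) | A vs C | B vs C | B vs A |
|---|---|---|---|
| 0 | 400 | 750 | 2,500 |
| 200 | 600 | 950 | 2,700 |
| 400 | 800 | 1,150 | 2,900 |
| 600 | 1,000 | 1,350 | 3,100 |

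The shift is the same for both arms. Leaving medicines out therefore lowers both arms' ratios and does not by itself favour the add-on.

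**The case against.** **The comparison with control has a purpose.** The main research question asks about a package combining service optimisation and community participation. That package is Arm B, and B versus control is its ratio. This stands: B versus control should be kept, and it is not a wrong quantity in itself.

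**Nothing is lost.** If costs and effects are reported by arm, B versus A follows by subtraction. This also stands, and it makes the fault easy to correct. But the plan does not commit to that ratio, and it lists the cost-effectiveness ratio as a primary outcome with control as the named comparator.

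**Excluding medicines may reflect a programme-cost perspective.** That is possible, since the text speaks of intervention inputs and government drug supply also reaches the control arm. No perspective is stated, however, and a programme-only view sits awkwardly with effects defined by medicine use and with ARS funds being directed to medicines. What remains is a request to state the perspective and show the effect of including medicines.

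**A stronger reading on extrapolation.** A reader might infer that the outcomes, "extrapolated at the population (NCD) level for the study arms", will be unweighted means from equal quotas per distance band, because "from each cluster, one village was randomly chosen" whatever the band's size. The documents do not support that. They do not say that unweighted means will be used, and survey weights are a detail an article may leave to the full plan. The quotas bear mainly on the consumption outcome. An uneven level of PHC use across bands would not by itself bias a difference between arms, because the intervention effect would have to vary with distance. That inference is not part of this point.

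**Conclusion.** The comparator point holds. As written, the plan commits to ratios against control and to no ratio for the community add-on, although the arms are nested. When the add-on is less efficient than Arm A, or Arm A dominates B, B versus control understates what the add-on costs per unit gained.

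The size cannot be computed from the documents. Under the assumed figures the understatement runs from a factor of 6.1 (B effect of 110) to 1.1 (B effect of 200) and disappears at 225.

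Two stronger conclusions are tempting. One is that the analysis will make an inefficient add-on look cost-effective. That needs a threshold, which the documents do not give, and an inefficient add-on, which is not known. The other is that leaving out medicines favours Arm B's add-on. It lowers the ratios of both arms, by an amount that depends on the unstated perspective.

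The comparator should be changed. The treatment of medicine costs should be stated and tested.

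**What to change.** 1. In the Cost-effectiveness analysis section, order the three arms by cost and check for dominance, including extended dominance. Report A versus control and B versus A as the incremental ratios. Keep B versus control, labelled as the ratio for the combined package. If the add-on proves more efficient than Arm A, Arm A is extendedly dominated and B versus control becomes the relevant ratio.
2. State the costing perspective. Include the cost of additional NCD medicines dispensed, at least as a sensitivity analysis: extra units dispensed multiplied by the indenting price.

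**Cost.** The first change needs no new data. For the second, the Process documentation section already foresees quarterly recording of NCD medicines dispensed, and the Facility survey section says indenting prices were physically verified. It should be confirmed that dispensing is recorded in the same way in control PHCs, because the calculation needs the difference between arms. The downside is a less favourable ratio, and B versus A will be imprecise if the two arms differ little in effect.

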#### Outcome estimation

Outcomes (see Table 9) will be reported as effects of said interventions and represented as risk ratios and odds ratios with 95 % confidence interval.

**Table 9 Tab9:** Measures (indicators) for primary and secondary outcome of interest

Factors to be measured	Indicator
Primary outcome of interest	
Improved and continuous availability of generic drugs at PHC	Percentage of PHC where all generic medicines for NCD patients adequately available in last three months
Increased and regular access to quality medicines for patients with NCD	Percentage of NCD patients/patient groups visit intervention PHC in last three months
Out-of-pocket expenses among patients with NCD	Percentage reduction in median OOP expenditure on medicines per year among NCD patients.
The marginal cost of the intervention to that of the outcome	Incremental cost effective ratio
Improved compliance to standard treatment guidelines by the PHC	Percentage MOs followed prescription practices as per the standard treatment guidelines.
Improved demand of generic drugs among the patients	Percentage increase in patients availing generic drugs from the PHC compared to what it was at three months back
Improved utilization of medicines among NCD patients	Percentage of NCD patients/ patient groups obtained complete and regular medication for last three months.
Secondary outcome of interest	
Better coordination among health staffs with regards to NCD patient group formation	- Percentage increase in number of patient groups formed. - Percentage increase in number of new diabetes patients registered in last three months for a given PHC. - Percentage increase in number of new hypertension patients registered in last three months for a given PHC.
Better drug procurement	Percentage PHCs where drug procurement is up to date for the last quarter.
Conduction of NCD clinics	Percentage PHCs conduct NCD days in last three months
Better reporting and recording by the pharmacists at PHC	Percentage PHCs where medicines were dispensed as prescribed

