**Methods:**

This study aims to understand if (and how) a package of interventions targeting primary health centres and community participation platforms affect utilisation and access to generic medicines for people with non-communicable diseases in the current district context in India. This study will employ a quasi-experimental design and a qualitative theory-driven approach. PHCs will be randomly assigned to one of three arms of the intervention. In one arm, PHCs will receive inputs to optimise service delivery for non-communicable diseases, while the second arm will receive an additional package of interventions to strengthen community participation platforms for improving non-communicable disease care. The third arm will be the control. We will conduct household and facility surveys, before and after the intervention and will estimate the effect of the intervention by difference-in-difference analysis. Sample size for measuring effects was calculated based on obtaining at least 30 households for each primary health centre spread across three distance-based clusters. Primary outcomes include availability and utilisation of medicines at primary health centres and out-of-pocket expenditure for medicines by non-communicable disease households. Focus group discussions with patients and in-depth interviews with health workers will also be conducted. Qualitative and process documentation data will be used to explain how the intervention could have worked.

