#### Research questions

The main research question of the study is: *does a package of interventions involving health services optimisation and strengthening community participation platforms at primary care level improve availability*, *affordability*, *utilisation and compliance of good quality generic drugs for NCDs in government facilities in Karnataka*? *If yes*; *how*, *and for whom and under what conditions does this happen*? We further developed five specific sub-questions in line with the main research question (and our study objectives listed above) as follows:Does optimisation of health services (announcing monthly NCD clinic days, increasing consultation time, providing counselling services and ensuring continuity of care) improve utilisation of drugs and their compliance among patients with NCDs?How can existing community participation arrangements be strengthened to form pressure groups of patients with chronic diseases at PHCs? Does this improve availability of drugs at these PHCs?If NCD patients shift or opt for public sector generic drugs for NCD care, will their OOP expenditure on NCD medicines and proportion of total household expenditure (THE) spent on NCD drugs decrease?Does the routine monitoring of the quality of NCD drugs strengthen the regulation of other drugs? How does the quality of drugs provided in government hospitals compare with those commonly bought over-the-counter in private pharmacies?How do private pharmacies respond to improved generic drugs availability and utilisation in government PHCs? Do the mean prices of essential NCD drugs and their availability change in response to improved availability of these in PHCs?What is the marginal cost of strengthening health systems so that access to medicines can be improved?

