#### Quantitative data and tools

##### Household survey tool

The household survey tool was based on the standardised WHO tool to conduct household survey and measure access and use of medicines based on a standardised WHO tool included in the WHO Operational Packages for Monitoring and Assessing Country Pharmaceutical Situations (World Health Organization [39]; see Additional file 4). The tool measures basic demographic and household characteristics, people’s health seeking behaviour, availability of medicines at homes, cost, affordability and appropriate usage of medicines by the NCD patients in these households. The questionnaire was adapted to suit the local context by choosing modules relevant to our study as well as adapting it for NCDs (the tool is originally designed for communicable diseases). Our final tool was divided into six parts to collect routine demographic information, health seeking behaviour, socio-economic status, perceptions on price and quality of NCD drugs and access to and use of medicines for NCD. We added additional questions to collect data on utilisation of PHC services for NCD, out-of-pocket (OOP) expenditure on NCD drugs, proportion of total health expenditure (THE) on NCD drugs, compliance with medication and awareness on generic drug availability at PHC.

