#### Covariate-adjusted analyses

This analysis will aim at establishing the improvements (in terms of outcome variables) due to the intervention. We will take into account the non-equivalence of the three intervention groups with respect to some baseline characteristics. This will be examined through logistic regression. Robust standard errors will be adjusted for clustering at village level. We will check and compare adjusted and unadjusted odds ratio while doing the logistic regression.

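### The reporting rule for Table 9 (risk ratios and odds ratios) does not fit the primary outcome on median out-of-pocket expenditure, and the planned difference-in-difference analysis is given no scale that would fit it.

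*Protocol article*

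**What the plan says.** All places are in the protocol article.

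- **Outcome estimation.** The sentence introducing Table 9 says that outcomes "will be reported as effects of said interventions and represented as risk ratios and odds ratios", with 95% confidence intervals. It makes no exception.
- **Table 9, primary outcomes.** The indicator for OOP expenses is "Percentage reduction in median OOP expenditure on medicines per year among NCD patients".
- **Abstract, Methods.** The primary outcomes include "out-of-pocket expenditure for medicines by non-communicable disease households". The same paragraph says that effects will be estimated by difference-in-difference.
- **Covariate-adjusted analyses.** The section states its purpose as follows: "This analysis will aim at establishing the improvements (in terms of outcome variables) due to the intervention". After referring to baseline non-equivalence of the arms, it says "This will be examined through logistic regression", and it compares adjusted with unadjusted odds ratios. No other regression model is named.
- **Difference in difference analysis.** This method is to test the effect of the intervention. No model, link, summary measure or scale is given.
- **Affordability share.** The Research questions ask whether OOP expenditure falls and also whether the "proportion of total household expenditure (THE) spent on NCD drugs decrease". The Household survey tool section says that data were added on the "proportion of total health expenditure (THE) on NCD drugs".

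**The concern.** The article fixes one pair of effect measures for a table whose primary rows include a median of a money amount. A risk or odds ratio needs a yes/no outcome, and no cut-off is given that would make OOP one. If the rule is followed as written, the reported effect is not the indicator that Table 9 promises. If it is not followed, the article leaves open which quantity will be reported.

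OOP expenditure is the affordability outcome of the study. It is primary in both the abstract and Table 9, and one of the research sub-questions is about it. If the scale is left open until endline data are in hand, the choice among several legitimate contrasts can be influenced by the results.

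A smaller problem touches the same sub-question. The share of expenditure that goes on NCD drugs has two denominators under one abbreviation.

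**Working it through.** **Inputs.** The article gives no baseline median, spread, target effect, alpha or power for OOP, so there is no stated OOP figure to reproduce. Its one design figure checks out (30 households × 39 PHCs = 1170 planned; 326 + 482 + 261 = 1069 surveyed) but does not bear on this point. All money amounts and spreads below are assumptions, used only to show how the measures relate.

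**Step 1. Does an odds or risk ratio determine the fall in the median?** Assume log-normal OOP with equal log-SD σ in both groups, and call spending high if it exceeds the control median.

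- Control: P(high) = 0.5, so the odds are 1.
- Take OR = 0.50. The intervention odds are 0.5, so P(high) = 0.5/1.5 = 1/3 and RR = (1/3)/0.5 = 0.67.
- On the log scale the intervention median lies below the control median by σ × z, where z is the standard normal 2/3 quantile, about 0.431.
- Reduction in the median = 1 − exp(−0.431σ).

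| Assumed σ | OR | RR | Reduction in median |
|---|---|---|---|
| 0.5 | 0.50 | 0.67 | 19.4% |
| 1.0 | 0.50 | 0.67 | 35.0% |
| 1.5 | 0.50 | 0.67 | 47.6% |

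The same OR and RR fit very different values of the Table 9 indicator. It cannot be recovered from them.

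**Step 2. Would difference-in-difference on means recover it?** For log-normal spending, mean = median × exp(σ²/2). Let the median fall by 20% and the log-SD move from 1.0 to σ₁. The change in the mean is 0.8 × exp((σ₁² − 1)/2) − 1.

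- σ₁ = 1.2: 0.8 × exp(0.22) − 1 = −0.3%
- σ₁ = 1.0: 0.8 − 1 = −20.0%
- σ₁ = 0.8: 0.8 × exp(−0.18) − 1 = −33.2%

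The two agree only if the spread does not change.

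**Step 3. Is the between-arm contrast on medians settled?** Assume intervention medians of 3000 falling to 2000 and control medians of 2400 falling to 1900.

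- Percentage reductions: 1 − 2000/3000 = 33.3% and 1 − 1900/2400 = 20.8%. The difference is 12.5 percentage points.
- Ratio of endline-to-baseline ratios: (2000/3000)/(1900/2400) = 0.84.
- Difference of absolute changes: −1000 − (−500) = −500 currency units.

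Each is a defensible difference-in-difference on medians, and none is an RR or OR in the sense of the Outcome estimation section. The article does not say which is meant.

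**Step 4. The two meanings of THE.** Assume drug spending of 700, total health spending of 1000 and total household spending of 10,000. Drug spending halves to 350, other health spending stays at 300, and total household spending is held at 10,000.

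- Health share: 700/1000 = 70%, then 350/650 = 54%.
- Household share: 700/10,000 = 7%, then 350/10,000 = 3.5%.

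The household share halves, while the health share falls by less than a quarter in relative terms. The denominator changes the answer.

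**The case against.** The strongest reply is that the article does plan a method that can handle expenditure. Difference-in-difference is the abstract's effect estimator, it contrasts arms by construction, and its scale is a detail that an article may leave to an analysis plan. That stands. A reader might infer that no suitable analysis of OOP exists, or that the within-arm wording of the indicator means no between-arm comparison is intended. The documents support neither. They also do not say that the difference-in-difference is linear or on means, so Step 2 is a warning about one possible version and not a criticism of a stated one.

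It can also be said that the ratio sentence is loose shorthand. Table 9 lists the incremental cost-effectiveness ratio as primary too. That cannot be a risk or odds ratio, and it has its own analysis section. The logistic sentence follows a remark on baseline non-equivalence and does not name OOP. A reader might infer that OOP will be dichotomised, but nothing in the article proposes this.

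What survives is the rule as written. It is unqualified and covers the OOP row. Unlike the cost-effectiveness ratio, OOP has no section of its own that overrides the rule. A fuller analysis plan would have to contradict the sentence, not merely add to it.

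On THE, a reader might infer that the health share could stay flat while drug spending halves. That happens only if other health spending halves as well (350/500 = 70%), and nothing in the documents suggests it. The share is also not a Table 9 outcome, and the questionnaire itself is not shown.

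**Conclusion.** The point holds in a limited form. The article assigns a primary outcome an effect measure that cannot express it, and it gives the one planned method that could express it no scale. This is a rule stated wrongly, not an omission that an unseen analysis plan would excuse.

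The mismatch itself needs no assumption, because it follows from the sentence and the Table 9 row. Its illustrated size (19.4% to 47.6% for one odds ratio, and −0.3% to −33.2% in the mean for one fall in the median) rests on assumed log-normal spending and assumed spreads. The article supplies no OOP data to replace them.

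The THE inconsistency is literal and real, but secondary.

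**What to change.** 1. In Outcome estimation, restrict risk and odds ratios to the binary indicators.
2. For OOP, keep the planned difference-in-difference and state its estimand on the median scale for each comparison with the control arm. Options are the ratio between arms of endline-to-baseline medians, the difference between arms in percentage reduction, or a quantile difference-in-difference. The first two share a null value but are different numbers (0.84 and 12.5 points in Step 3), so name one as primary. Both need a baseline median above zero, which can be checked in the baseline data already collected.
3. Take the 95% confidence interval from a bootstrap that resamples PHCs, the randomised unit, keeping each household's two surveys together.
4. If means are preferred, on a log or ratio scale, reword the Table 9 indicator to match.
5. Give THE one meaning. The research question names household expenditure, so use that denominator, or restate the question if the tool captured only health expenditure.

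A median regression of endline OOP conditional on baseline OOP is not a direct substitute, because its coefficient is not in general the Table 9 quantity.

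The cost is a change of wording and slightly more programming. The OOP fix needs no new data, since the household tool collects OOP and the same households are to be surveyed at endline.
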